#### 2.4.2. Psychological well-being

The secondary endpoint evaluates whether the PICMOA intervention effects social and psychological properties including mental status, well-being, loneliness, and social connectedness. The Japanese version of the Geriatric Depression Scale-short form (GDS-15) (Sugishita et al., 2017) is used to assess mental status. The GDS-15 is a common 15-item depression screening scale that showed high validity and reliability among Japanese older population. The score ranges from 0 to 15 with higher scores indicating a more depressed mood. The 5-item World Health Organization Well-Being Index (WHO-5) (Inagaki et al., 2013) is used to assess subjective psychological well-being. The WHO-5 has adequate validity and has been used as an outcome measure in clinical trials (Topp et al., 2015). The percentage score of WHO-5, ranging from 0 to 100, is calculated based on the raw score multiplied by 4. Additionally, the Health Utilities Index Mark 3 (HUI3) (Horsman et al., 2003; Noto and Uemura, 2020) is introduced to evaluate the health-related quality of life (HRQoL). The HUI3 classification system comprises eight components, including vision, hearing, speech, ambulation, dexterity, emotion, cognition, and pain, with five or six levels of ability/disability for each. HUI3 introduces the single- and multi-attribute utility scoring systems. The single-attribute utility score ranges from 0.00 to 1.00 in each component and multi-attribute utility score of overall HRQoL ranges from −0.36 to 1.00.

We use the Multidimensional Scale of Perceived Social Support (MSPSS) (Zimet et al., 1988; Iwasa et al., 2007) and UCLA Loneliness Scale-10 item version (Arimoto and Tadaka, 2019) for social support network and perceived loneliness, respectively, to assess the social aspects. The MSPSS is a 12-item scale. Total score and subscale-scores regarding support from family, friends, and significant others can be calculated by the average of each score, ranging from 0 to 7 where higher score implies stronger support. Loneliness is measured using a 10-item version of the revised UCLA Loneliness Scale which assesses the frequency of feeling lonely with 4 choices per item: (1) never, (2) rarely, (3) sometimes, and (4) always. The total score can range from 10 to 40 with higher score indicating severe loneliness.

During the intervention period, participants are required to answer the 6-point smiley face Likert scale before and after each PICMOA or health education session to evaluate the immediate psychological change.

### 2.5. Sample size

Based on our prior RCT study using group conversation intervention, we hypothesized the small to medium effect size of the PICMOA intervention on the verbal fluency tests, which measure the cognitive outcomes in this study. We used G^*^power (Faul et al., 2007) for sample size calculation, with 80% power, small to medium effect size (f = 0.175), a two-sided hypothesis test, an analysis of variance model between groups over time, and an alpha level of 5%. The sample size calculation showed that we needed a total of approximately 80 participants considering a 15% drop out. Eighty-one participants were included in the trial and allocated to the intervention or control groups.

### 2.6. Data management and monitoring

The research staffs manage all data including the results of neuropsychiatry tests and questionnaires. Data entry will be outsourced to a third party. All records of nonadherence and drop-out will be electronically documented. Anonymized data stored on a secure computer will be used for analysis, and the data with personal information will be kept in a locked cabinet in a secured office.

### 2.7. Statistical analyses

To estimate the effect of the PICMOA intervention, the linear mixed models with random intercepts for outcome measurements will be computed. The models will include the following independent variables: groups assignment factor (PICMOA group: 1, control group: 0), time factor (pre: 0, and post: 1), and their interaction term (time × group). The interaction term will be interpreted as the intervention effect. Given that some baseline statuses such as cognitive functioning, psychosocial status, and familiarity with using equipment may influence the effect of this social intervention, we will examine how much the intervention effects vary depending on the levels of these statuses.

All analyses will be performed using R software, and statistical significance threshold will be set as *P* < 0.05.

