**Figure 4 F4:**
[figure not shown]
Flow of the structured group conversation during the PICMOA intervention.

During the one-week preparation period for each intervention session, participants are instructed to take as many photos as possible in their daily life according to the theme of conversation for the next intervention session (e.g., favorite things, neighborhood landmarks) using the camera function in the intervention application. The list of 12 themes of conversation was described in our previous paper (Otake-Matsuura et al., 2021). Then, participants are required to register two photos, which they select from the photos they took during the 1-week preparation period via the application for the intervention session.

The participants join the conversation session in a small group of four people. The conversation system in the application is designed to start automatically on the participants' smartphone at the scheduled time. The group conversation program is structured into presentation and discussion parts. First, one participant presents (presenter) one photo for one minute which is displayed on all participants' smartphones through the application. Subsequently, all other participants ask questions about the photo, and the presenter responds to the questions in a natural conversation context for two minutes. Then, another photo is displayed, and participants continue presenting and discussing the new photo. After one participant presents two photos and all the other participants discuss it, the role of presenter is switched to another participant and the same process is repeated so that participants experience two photos per presenter in one intervention session.

If a participant drops out after allocation to the intervention group, the intensity of the intervention, such as the number of pictures, intervention time, and the number of people to talk to, will change. The bias resulting from inconsistent intervention intensities across groups could directly affect the results and effect sizes. Therefore, in cases where a participant drops out, older volunteers or research staff participate in the intervention session as a substitute to control the intensity of the intervention.

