On the other hand, control group participants attend an active control, which is a weekly health education video on the tablet (Lenovo YT-X705L). All participants in the control group are required to watch the health education videos about successful aging for approximately 30 minutes via a webinar (https://zoom.us/) once a week for 12 weeks. Health education videos are provided in a noninteractive way with the participants' cameras and microphones turned off throughout.

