#### 2.3.3. Randomization

Stratified randomizations were performed using a permuted block with a 1:1 allocation to one of the two groups: (1) intervention group with PICMOA and (2) control group with health education. Participants were stratified according to sex and sorted based on the TICS-J total scores. Then, permuted block randomization, with a block size of 2, was performed to allocate participants to the group using computer-generated random numbers. The individual in charge of allocation only had access to the following information during the randomization process: ID, TICS-J scores, and sex. All randomization processes were conducted using statistical software R.

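### PICMOA is delivered in conversation groups of four, but neither the stated model nor the sample size allows for correlation within those groups

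*Protocol article*

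**What the plan says.** Allocation is individual. Within sex strata, participants were sorted by TICS-J score, and "permuted block randomization, with a block size of 2, was performed to allocate participants to the group" (section 2.3.3).

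Delivery differs between the arms (section 2.2). For PICMOA, "The participants join the conversation session in a small group of four people"; members present photos to each other and answer each other's questions. If someone drops out, a volunteer or staff member takes the seat so that intensity stays constant. For controls, "Health education videos are provided in a noninteractive way", with cameras and microphones off.

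The analysis (section 2.7) is stated as "the linear mixed models with random intercepts for outcome measurements will be computed". The fixed part is arm, time (pre, post) and arm by time, and "The interaction term will be interpreted as the intervention effect". The unit of the random intercept is not named.

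The sample size (section 2.5) uses "an analysis of variance model between groups over time", with f = 0.175, 80% power, two-sided alpha of 5% and 15% drop-out, giving about 80 participants; 81 were allocated. It gives no ICC or design effect.

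**The concern.** This is a partially nested trial: about ten conversation groups of four in one arm against about 40 individually treated people in the other. The exchange between group members is itself the treatment, so members may improve or decline together. Section 2.2 recognises the conversation group as a source of variation, since it warns that uneven intensity between groups could affect results and effect sizes. Holding the group at four seats makes intensity more even, but it does not remove dependence among people who talk to each other.

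With two measurements per person, the natural reading of the random intercept is one per participant. That handles the pre-post correlation but not correlation between conversation partners. If such correlation exists, the interaction's standard error is too small, its confidence interval too narrow, and the stated power too high.

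**Working it through.** **Inputs.** From the article: group size 4; 81 participants allocated 1:1, so about 40 per arm and about 10 groups; f = 0.175; alpha 5% two-sided; power 80%; drop-out 15%. Assumed, because the article does not give them: pre-post correlation ρ = 0.5, and an ICC of the pre-post change within conversation groups of 0.05 to 0.20.

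**1. The plan's own figure.** For the within-between interaction with two arms and two times, the noncentrality is λ = f² x N x 2/(1 − ρ). With N = 68 and ρ = 0.5, λ = 0.030625 x 68 x 2/0.5 = 8.33 on 1 and 66 degrees of freedom, and power is 81.2%. Then 68/0.85 = 80, which reproduces the stated size. Other correlations do not reproduce it (ρ = 0.4 gives 95, ρ = 0.6 gives 64). No design effect was needed, so the figure is consistent with independent participants. The implied effect is 2f x √(2/(1 − ρ)) = 0.35 x 2 = 0.70 SD of change.

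**2. Variance of the arm contrast.** The PICMOA mean is inflated by 1 + (4 − 1) x ICC and the control mean by 1. With equal arms, the contrast is inflated by ((1 + 3 x ICC) + 1)/2 = 1 + 1.5 x ICC.

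**3. Type I error and power.** Type I error was simulated for the change-score test that matches the stated model on complete data (10 groups of 4 against 41 individuals, simple randomisation, 200,000 trials per ICC). Power uses 34 evaluable per arm and the normal approximation Φ(0.70 x √(34/2)/√(1 + 1.5 x ICC) − 1.96).

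| ICC | Contrast variance factor | True SE / model SE | Type I error, stated model | Power, clustering allowed for |
|---|---|---|---|---|
| 0 | 1.000 | 1.000 | 5.0% | 82.3% |
| 0.05 | 1.075 | 1.037 | 6.0% | 79.5% |
| 0.10 | 1.150 | 1.072 | 6.9% | 76.8% |
| 0.20 | 1.300 | 1.140 | 8.7% | 71.6% |

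At ICC 0.01 and 0.02 the type I error is 5.1% and 5.4%. A test on conversation-group means with Satterthwaite degrees of freedom stays at 5.0% to 5.1% over the tabulated range. The approximation is about one point optimistic at ICC 0 (82.3% against the exact 81.2%), so power at ICC 0.05 is nearer 79%.

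**4. The allocation scheme.** Sorting by TICS-J and allocating in pairs nearly equalises baseline TICS-J between arms, and the stated model takes no account of it. For TICS-J the true contrast variance, relative to what the model assumes, is about (1 − ρ²)/(2(1 − ρ)) = (1 + ρ)/2 = 0.75 at ρ = 0.5. Adding 1.5 x ICC gives 0.825, 0.90 and 1.05 at ICC 0.05, 0.10 and 0.20. From 2(1 − Φ(1.96/√factor)), type I error is 2.4% at ICC 0, then 3.1%, 3.9% and 5.6%. Simulation with the sorted allocation gave 2.4%, 3.3%, 3.9% and 5.5%. At ρ = 0.7, simulation gave 3.6%, 4.4%, 5.2% and 6.9%. For an outcome correlated 0.4 with TICS-J (ρ = 0.5), it gave 5.3%, 6.2% and 7.9% at ICC 0.05, 0.10 and 0.20, so the offset is small there.

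**The case against.** The strongest objection is that the excess is conditional. No ICC is given. Under a strict null, where the sessions affect nobody and groups formed after randomisation share nothing else, the ICC is zero and the test holds its 5%. Fixed time slots, automatic moderation and substitutes are meant to make sessions uniform, and outcomes are rated by telephone by blinded assessors. These features argue against taking 0.20 as typical, but they do not make the ICC zero. This part stands, and the point has to be put conditionally.

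A reader might infer that every outcome is tested too liberally. The documents do not support that, because for TICS-J, one of the primary measures, the sorted block-of-2 allocation makes the same test conservative at small ICC. A reader might also infer that the same four people stay together for all 12 weeks. The substitute rule suggests stable groups, but the article does not say so.

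Substitutes are not randomised participants, so with 15% drop-out the analysed groups average 4 x 0.85 = 3.4 members. The contrast factor is then nearer 1 + 1.2 x ICC, which at ICC 0.20 gives √1.24 = 1.11 for the SE ratio instead of 1.14. The upper end of the range is therefore somewhat generous.

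Finally, this is a condensed article, and a fuller plan may hold more random-effect structure. That lowers certainty. It does not remove the point, since section 2.7 states the model's terms and conversation group is not among them.

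**Conclusion.** The point holds conditionally. The design is partially nested, and neither the stated model nor the stated sample size provides for it. If changes correlate within conversation groups, the standard error of the arm contrast is understated by about 4% to 14% for an assumed ICC of 0.05 to 0.20. Type I error is then about 6% to 9% for outcomes not closely tied to TICS-J, and somewhat less for outcomes moderately correlated with it. For TICS-J the allocation scheme offsets much or all of the excess. The stated 80% power is met only if clustering is negligible.

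The conclusion that type I error does exceed 5% goes further than the documents allow. They make a positive ICC plausible but give no value. The power figures also rest on a pre-post correlation of 0.5, which is unstated but is the value that reproduces the planned size. Severity: should be fixed before analysis.

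**What to change.** Before results are seen, add to section 2.7 a random effect for conversation group that acts on the post-intervention measurement in the PICMOA arm only, with each control as a singleton. Use Satterthwaite or Kenward-Roger degrees of freedom, and report the estimated ICC for each outcome. If group membership changed during the 12 weeks, assign each participant to the group attended most often, or use a multiple-membership term.

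In section 2.5, state that the 80% power assumes no clustering and give the range over ICC 0.05 to 0.20. Recruitment is complete, so this is disclosure and enrolment need not change.

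The cost is small. Session scheduling should already supply group membership. Intervals will be slightly wider, and a variance component from about ten groups of at most four will be imprecise and may be estimated at zero.

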#### 2.3.2. Procedure

In the recruitment phase, the municipality government sent recruitment letters to community dwelling older adults, who responded to previous surveys of the municipality and do not have long term care certification, by mailing them in several batches. We also posted flyers on the city's website and placed flyers at city stores. Once our research staffs were contacted by potential participants who expressed their interest in the trial, the eligible participants were required to provide their written informed consent if they agreed to participate after the explanation of the research. The inclusion and exclusion criteria except for the scores of TICS-J were screened at this point.

After obtaining informed consent to participate, questionnaires and standardized neuropsychological batteries were administered as baseline assessments. Based on the scores of TICS-J in the baseline assessment, final screening was done to proceed to the randomization step.

Following the allocation, a letter was sent to each participant to inform them of the group allocation. Next, participants practiced using the equipment (smartphone/ tablet) with the provided manual and timely instruction from research staff, and experienced a test session of PICMOA/health education once. Then, they started the intervention phase for 12 weeks.

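### The planned interaction test is in effect a change-score comparison: unbiased and consistent with the sample size, but less precise than adjusting each outcome for its own baseline

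*Protocol article*

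**What the plan says.** Section 2.7 of the Protocol article states that "the linear mixed models with random intercepts for outcome measurements will be computed". The fixed effects are "groups assignment factor (PICMOA group: 1, control group: 0), time factor (pre: 0, and post: 1", together with their product, and the reading is explicit: "The interaction term will be interpreted as the intervention effect". Pre and post scores are both responses, and the group term is the difference between arms at baseline, which the model estimates freely.

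Baseline status appears once more in 2.7, as a possible effect modifier: "we will examine how much the intervention effects vary depending on the levels of these statuses". No baseline covariate and no common baseline mean is stated for the main effect.

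Three other places bear on the point.
- Section 2.3.2 puts the baseline assessment before allocation: "Based on the scores of TICS-J in the baseline assessment, final screening was done to proceed to the randomization step".
- Section 2.3.3 stratifies by sex, sorts participants on total TICS-J and allocates 1:1 in blocks of 2.
- Section 2.5 sizes the trial on a group-over-time analysis of variance "with 80% power, small to medium effect size (f = 0.175), a two-sided hypothesis test", with alpha 5% and 15% dropout, giving about 80; 81 were allocated.

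**The concern.** Because baseline is measured before randomization, the two arms have the same expected baseline for every outcome. A model that still estimates a baseline group difference spends information on a quantity known to be zero in expectation. With only a pre and a post score, the interaction then reduces to the difference in mean change. That contrast subtracts the whole baseline score, whereas the efficient adjustment subtracts only the part that predicts the post score.

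At stake is precision, for the cognitive tests and the psychosocial scales alike. Recruitment is closed (2.3.1) and the Discussion says the size was set by feasibility, so the analysis model is one of the few remaining ways to narrow the confidence intervals. For outcomes not used in the sorting, a chance baseline difference also enters the change score in full and returns partly as regression to the mean. TICS-J raises a separate question, because its baseline value was both the entry screen (at least 33) and the sorting variable for allocation.

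**Working it through.** **1. Reproduce the planned size.** Inputs from 2.5: f = 0.175, power 80%, two-sided alpha 5%, 15% dropout; two groups and m = 2 time points. For the group-by-time test, the noncentrality is λ = f²·N·m/(1−ρ), with 1 and N−2 degrees of freedom. The article gives no ρ.

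| ρ (assumed) | N completers | N with 15% dropout |
|---|---|---|
| 0.3 | 92 | 109 |
| 0.5 | 68 (power 0.812) | 68/0.85 = 80 |
| 0.7 | 42 | 50 |

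Of these, only ρ = 0.5 gives the stated total of about 80. The between-group version of the test would need 196 at ρ = 0.5. So ρ ≈ 0.5 is an inference from N.

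**2. The planned effect in SD units.** For a difference in change Δ (in SD), the squared noncentrality of the t test is N·Δ²/[8(1−ρ)]. Setting this equal to 2f²N/(1−ρ) gives Δ = 4f = 4 × 0.175 = 0.70 SD.

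**3. The planned estimator is the change-score contrast.** In simulated trials (n = 80, ρ = 0.5, complete data) the interaction and the two-sample change-score comparison agreed to four decimals, with mean standard error 0.228 for both. Analysis of covariance (ANCOVA) gave 0.195 and a mixed model with a common baseline mean 0.194. With 15% of post scores missing, the mixed model and the completers' change score differed slightly (0.233 and 0.237); ANCOVA gave 0.204. Only 12 trials were run per setting, so these are rough apart from the identity, which is algebraic.

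**4. Size of the loss, equal pre and post variances.** Per participant, Var(change) = 2(1−ρ)σ² and Var(ANCOVA) = (1−ρ²)σ², so the ratio is (1+ρ)/2. Power is from the noncentral t at 68 completers, Δ = 0.70 SD, with 66 and 65 degrees of freedom.

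| ρ | Variance ratio | SE reduction | Power as planned | Power adjusted |
|---|---|---|---|---|
| 0.3 | 0.65 | 19% | 67% | 85% |
| 0.5 | 0.75 | 13% | 81% | 91% |
| 0.7 | 0.85 | 8% | 96% | 98% |
| 0.8 | 0.90 | 5% | over 99% | over 99% |

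At ρ = 0.5 the completers needed fall from 68 to 52 (80 to 62 with dropout).

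**5. TICS-J: effect of the cut at 33.** Selecting on baseline leaves the regression slope b unchanged and shrinks the baseline variance Vx. The ratio becomes Ve/[Ve + (1−b)²Vx], where Ve is the residual variance. Assume normal scores, b = 0.5, Ve = 0.75 and 20% screened out (the article does not give this fraction). Then Vx = 0.583 and the ratio is 0.75/(0.75 + 0.25 × 0.583) = 0.84, an SE reduction of 8.5%. Without truncation it is 13.4%; with 10%, 30% and 50% screened out it is 10.1%, 7.3% and 5.6%. At 20% the observed ρ drops to 0.40, for which (1+ρ)/2 would give 0.70; that formula does not apply, because the pre and post variances are no longer equal.

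**6. TICS-J: effect of the sorted allocation.** Pairing on baseline nearly removes the baseline difference, so the true SE of the change contrast is close to that of ANCOVA. At 68 participants this is √(4 × 0.75/68) = 0.210. The planned model still reports √(4 × 1/68) = 0.243 untruncated, or √(4 × 0.896/68) = 0.230 with 20% screened out. The type I error at nominal 5% is then about P(|Z| > 1.96 × 0.243/0.210) = 2.4%, or 3.2% truncated. Simulation of sorted pairs (6,000 trials per setting, sex omitted) gave 2.7% and 3.0% at 68 participants, against 5.2% and 4.7% for ANCOVA.

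**The case against.** The strongest reply is that nothing here is wrong. Under randomization the interaction is unbiased, the sample size was computed for that same contrast, and on its own assumptions the plan reaches its 80% power. All of this stands, and it settles the label: the point concerns efficiency.

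The gain also depends on a correlation that the article does not report. If ρ is 0.7 or 0.8, power is already 96% or higher and little is gained beyond somewhat narrower intervals. This limits the size, but the gain stays positive throughout the range. It is largest if ρ falls below the planning value, where the planned test would be underpowered.

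A reader might infer that TICS-J suffers most, because truncation lowers its pre-post correlation. The documents do not support that. Selecting on baseline shrinks the loss (step 5), and the sorted blocks of 2 make the two TICS-J point estimates almost equally precise (step 6). Nor does regression to the mean from a chance imbalance matter much for TICS-J; that argument belongs to the outcomes not used for sorting.

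Finally, one might read the effect-modification sentence in 2.7 as supplying baseline adjustment. It asks whether the effect varies with baseline and leaves the main-effect model unchanged.

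**Conclusion.** The point holds as a free improvement. As written, 2.7 commits the trial to what is essentially a change-score comparison and forgoes precision available from baseline data already collected. At the inferred ρ of 0.5 the standard error would be 13% smaller and power for the planned effect 91% instead of 81%; over ρ from 0.3 to 0.8 the reduction runs from 19% to 5%. These figures assume equal pre and post variances, 68 completers and an effect of 0.70 SD.

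For TICS-J the finding is different: the model omits the variable on which allocation was sorted, so its standard error is overstated and its test conservative, with type I error of about 2 to 3%. This rests on an assumed slope of 0.5, normal scores and, for the truncated case, 20% screened out.

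A reader might go further and call the planned analysis biased, invalid or inconsistent with the sample size. The article supports none of these.

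**What to change.** Before analysis, make the baseline-adjusted post-intervention difference the primary estimate for each outcome, in one of two ways:

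- keep the mixed model but drop the group main effect, so that both arms share a baseline mean, with an unstructured 2 × 2 covariance. This retains participants with only one measurement and allows the TICS-J pre and post variances to differ;
- or use ANCOVA of the post score on group and the outcome's own baseline.

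In either case include the allocation factors, sex and baseline TICS-J. When TICS-J is itself the outcome, its own baseline already serves. Keep the planned interaction model as a sensitivity analysis.

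The cost is a short change to the model specification and no new data. Because the model is published, the trial is open-label and the second intervention phase was under way, the change should be a dated, documented amendment made before outcomes are compared by arm.
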